### 5.3 Protocol deviations

Protocol deviations were defined as noncompliance with the clinical trial protocol, the approved Human Research Ethics Committee protocol, or the guidelines for Good Clinical Practice in Australia. Protocol Deviations are reported to the Data Safety and Monitoring Board and Human Research Ethics Committee. The number of trial participants withdrawn from the study, discontinued from the study medication, and unblinded, will be reported. Serious deviations from the protocol will be reported where they potentially impact on the integrity of the trial data, and, if necessary, sensitivity analysis will be performed to assess their impacts.

### 5.4 Outcome definitions

#### **Primary outcome**

Reported days of methamphetamine use: The primary outcome is change in self-reported days of methamphetamine use in the past 4 weeks from baseline to weeks 4,8,12 and 20, assessed using the Timeline Followback (TLFB)[17], with week 12 being the primary endpoint.

Days when a participant is incarcerated or in hospital (inpatient only) are censored from the TLFB. The length of each assessment window can vary dependent on the actual follow-up date. For this reason an offset term will be included in the model to adjust for variation in the days observed in each assessment window.

TLFB data will be validated against biologically verified abstinence from methamphetamine use contained in oral fluid samples. Data on methamphetamine use from oral fluid samples was not complete at the time of writing this statistical analysis plan.

## **Secondary outcomes**

Abstinence from methamphetamine use: Methamphetamine-negative oral fluid samples (< 25 ng/mL methamphetamine) taken at weeks 4, 8 and 12 using a commercial oral fluid collection device. Oral fluid is a sensitive and stable medium for the detection of methamphetamine and correlates highly with plasma tests [18].

Depressive symptoms: Change in the total score on the Patient Health Questionnaire-9 (PHQ-9) [19] from baseline to weeks 4, 8, 12 and 20, with week 12 being the primary endpoint. The PHQ-9 is a brief 9-item questionnaire with scores ranging from zero to 27 (higher scores indicate more depression) [19].

Sleep quality: Change in total score on the Athens Insomnia Scale (AIS) -5 [20] from baseline to weeks 4, 8, and 12, with week 12 being the primary endpoint. The AIS is a 5-item self-report measure that gives scores from 0 to 15 with higher scores indicating more insomnia [20].

HIV risk behaviour: Change in the total score on a modified version of the HIV Risk-taking Behaviour Scale (HRBS) from the Opioid Treatment Index [21] from baseline to weeks 4, 8 and 12, with week 12 being the primary endpoint. The HRBS is a validated and reliable scale that provides a composite risk index for injecting and sexual behaviour. The modified version of this scale is available from the authors on request. The scores range from 0 to 22 with higher scores indicating more risk.

Quality of life: Change in the utility score on the EuroQol-5D-5L (EQ-5D) [22] from baseline to weeks 4, 8 and 12, with week 12 being the primary endpoint. Utility scores in this sample range from -0.138 to 1, with higher scores indicating better quality of life.

## **Tertiary/exploratory outcomes included in planned analysis**

Suicidality: A score of 3 or greater on the Columbia Suicide Severity Rating Scale Screener (CSSRS-S) [23, 24] at any time in the 12-week trial medication phase (i.e., wk 0 to wk 12).

Other substance use: Change in total days of use for other drug classes (tobacco, alcohol, cannabis, cocaine, ecstasy, hallucinogens, inhalants, and heroin) in the past 4 weeks from baseline to weeks 4, 8, 12 and 20, with week 12 being the primary endpoint. This gives a potential 224 days of other substance use (the range in this sample is 0 to 91).

Anxiety: Change in total scores on the Generalized Anxiety Disorder – 7 Item (GAD-7) [25] from baseline to weeks 4, 8 and 12, with week 12 being the primary endpoint. The GAD-7 is a validated screening tool for Generalized Anxiety Disorder that can also be used to assess the severity of anxiety [25]. Scores range from 0 to 21 with higher scores indicating more anxiety.

Participants impression on health status: The score on the single-item Patient Global Impression – Improvement (PGI - I) [26] at weeks 4, 8 and 12. The PGI provides a single score that reflects whether participants' perceive that their health status has improved since the start of the trial.

## Outcomes for which there are no planned analyses

Treatment satisfaction: Scores on the Treatment Satisfaction Questionnaire for Medication Version II (TSQM II) [27] at week 12 are being used to assess treatment satisfaction. The TSQM II provides a global satisfaction summary score and subscale scores for medication convenience, side-effects, and effectiveness. Additional unpublished questions have been included at other weeks to assess tolerability and expected reactions to mirtazapine (see Appendix for details).

Concomitant medications: All medications taken by participants during the trial are recorded on a template adapted from the National Institute of Health Concomitant Medications Form [28]. For each medication is coded against the WHO generic medication code and information is recorded on the dose, frequency and route.

Health Economics: Health economics data collected include: the EuroQol 5D – 5L [22] at baseline and weeks 4, 8 and 12; the Work Productivity and Activity Impairment Questionnaire – General Health (WPAIQ-GH) V2 [29] at week 12; and, contact with health services and the criminal justice system in the three months prior to baseline and from baseline to the week 12 assessment (collected at the week 12 assessment).

Adverse events (AEs): The percentage of participants reporting AEs, and serious adverse events (SAEs), by System Organ Classification, will be coded according to the Medical Dictionary for Regulatory Activities (MedDRA)[30]. AEs will be counted once only for a given participant.

Body Mass Index (BMI): BMI based on verified weight and height at eligibility and the final medical assessment.

## 6 Analysis

### 6.1 General approach to planned analyses

The analysis plan below is based on blinded data that did not include the treatment allocation variable. After unblinding, model assumptions will be checked (e.g., distribution of the outcome, cell sizes and model convergence and model fit) and models will be modified as necessary; any covariates that need to be included in the model will be identified.

Descriptive statistics will be presented as the mean (standard deviation) for continuous parametric measures and median (inter-quartile range) for highly skewed measures. Categorical variables will be presented as a percentage per category. Baseline descriptive statistics will be compared between the treatment conditions using appropriate inferential statistics. Bootstrapped confidence intervals will be used for outcomes that are highly skewed.

As a general principle, linear models will be used for normally distributed continuous outcomes. A logistic link will be used for categorical outcomes. A Poisson or negative binomial link will be used for count data and may be used for categorical outcomes with small cell sizes where this produces superior model fit. If model assumptions are breached, other model options will be examined to identify the best model fit.

A random intercept term for participant identifier will be included in all models with time-varying data model to account for clustering of data on repeated assessments. A random intercept for site will be included in models only if this significantly improves model fit (based on a likelihood ratio test;  $p < 0.05$ ).

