## 3.2 Randomisation

Eligible participants are randomly assigned (1:1) to receive either placebo or mirtazapine based on a computer-generated permuted block randomisation sequence with variable block sizes, stratified by site, sex (male vs. female or other) and depression (PHQ-9 score < 10 vs. 10 or greater) assessed at eligibility.

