## 5 Statistical Principles and definitions

### 5.1 Confidence intervals and p values

All tests will be two-tailed. Significance will be  $p < 0.05$  for all outcomes. Confidence intervals will be 95%.

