## 6.6 Additional analyses

The following analyses may be done after the primary analysis to supplement the primary analyses or as separate research papers.

Subgroup analyses: Subgroup analyses are planned for the sub-groups of (1) depressed (PHQ-9 score 10 or greater at eligibility), (2) not depressed (PHQ-9 score of < 10 at eligibility), (3) participants who reported being male at birth, and (3) participants who reported being female or other sex at birth. The randomisation was stratified on these subgroups, meaning that participants are randomly assigned to condition within each subgroup.

Per-protocol analysis: A set of per-protocol analyses will be undertaken on the per-protocol dataset. This may be done for the primary and secondary end-points and for any sub-group analyses. The per protocol analysis will use non-imputed data. These models will incorporate adjustment to account for any group differences in baseline characteristics.

Treatment complier effect: A set of treatment complier analyses may be conducted on the treatment complier dataset. This may be done for the primary and secondary endpoints and for any sub-group analyses. Treatment complier analysis will incorporate adjustment to account for any group differences in baseline characteristics.

Average treatment effect: Additional analyses may be conducted that repeat the primary and secondary analyses but which collapse the follow-up data across the week 4, 8 and 12 follow-up time points (i.e., baseline [0] vs. week 4 [1], week 8 [1], week 12 [1]) such that the outcome is the average treatment effect across the 12-week trial medication period.

Covariate adjustment. Analyses of the primary outcome measure will be repeated with adjustment for a set of prognostic variables, as per the recommendations of Kahan et al. [32], to improve model precision and aid interpretation of the main analyses of the primary outcome. These prognostic variables will include: age, sex (male vs. female or other), methamphetamine use days in the past 4 weeks at eligibility, main route of methamphetamine administration (injecting vs. other routes), and PHQ-9 depression score at eligibility. All of these variables were collected at the eligibility assessment, prior to randomisation, and therefore they are not collider variables.

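### The per-protocol and complier models take their covariates from observed baseline imbalance instead of a fixed prognostic list, and Section 6.1 plans significance tests of balance between randomised arms

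*Combined protocol and SAP*

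**What the plan says.** SAP Section 6.1 plans that "Baseline descriptive statistics will be compared between the treatment conditions using appropriate inferential statistics". It gives no threshold for these tests. Section 5.1 says "All tests will be two-tailed. Significance will be" p < 0.05 for all outcomes, so 0.05 for baseline variables is an assumption. Section 6.1 also says that after unblinding "any covariates that need to be included in the model will be identified", again without a criterion.

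Section 6.6 says of the per-protocol models: "These models will incorporate adjustment to account for any group differences in baseline characteristics". Of the complier models it says: "Treatment complier analysis will incorporate adjustment to account for any group differences in baseline characteristics". Neither paragraph lists variables, sets a threshold or asks whether a variable predicts the outcome.

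Under Covariate adjustment, the same section takes a different approach for the primary outcome: "Analyses of the primary outcome measure will be repeated with adjustment for a set of prognostic variables". The set is "age, sex (male vs. female or other), methamphetamine use days in the past 4 weeks at eligibility, main route of methamphetamine administration", plus the eligibility PHQ-9 score. No such list is given for the secondary outcomes.

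Section 3.2 says that allocation was "stratified by site, sex (male vs. female or other) and depression (PHQ-9 score < 10 vs. 10 or greater) assessed at eligibility". By contrast, the two supplementary datasets in Section 5.2 depend on events after randomisation. The per-protocol set drops data after permanent discontinuation for reasons unrelated to the medication. The complier set also drops assessment windows in which adherence was below the study median.

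**The concern.** Adjustment helps when the covariate predicts the outcome, and it removes confounding when the covariate also predicts who stays in the analysed set. How far the arms happen to differ on a variable shows neither. A rule driven by observed differences brings in variables that differ but do not matter. It leaves out variables that matter when their imbalance is not conspicuous. Because group differences are visible only once allocation is known, the choice is also made after unblinding.

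In the per-protocol and complier sets the differences need not be chance. If discontinuation or adherence depends on a prognostic characteristic differently in the two arms, the comparison is confounded, and a selector that often misses that characteristic leaves bias behind.

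The Section 6.1 tests are a smaller, related matter. Between properly randomised arms they answer no open question, and their p-values invite readers to conclude that randomisation worked or failed.

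**Working it through.** The plan states no figure on this point, so there is none to reproduce. Three checks follow.

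**1. False differences between randomised arms.** Inputs: alpha 0.05 (assumed to apply), and k tests counted from Tables 5 and 6. Table 5 has 18 row headings. It has 24 measures if the five living-arrangement items and three treatment-history items are tested separately. The total is 31 with the seven Table 6 outcomes that can be tested at baseline. Expected false differences = 0.05k; chance of at least one = 1 - 0.95^k if the tests are independent.

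| k | Expected | At least one |
|---|---|---|
| 18 | 0.90 | 60% |
| 24 | 1.20 | 71% |
| 31 | 1.55 | 80% |

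If selection were by such a test in the full randomised arms, each of the five named prognostic variables would be picked about 5% of the time, however prognostic it is. The chance that none is picked is about 0.95^5 = 77%. Sex should be picked less often, because it is a stratification factor.

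**2. Selection after randomisation.** This is a simulated linear outcome with one follow-up value and no true effect: 339 participants, 24 independent covariates of which one is prognostic (assumed correlation 0.5), and about half the sample retained. Retention in the active arm depends on the prognostic covariate. There were 4,000 runs per row. Bias is in SD units.

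| Selection | Prognostic covariate picked at p < 0.05 | Bias, unadjusted | Bias, test-selected | Bias, fixed |
|---|---|---|---|---|
| Weak | 16% | -0.074 | -0.044 | 0.000 |
| Moderate | 45% | -0.136 | -0.044 | 0.003 |
| Strong | 80% | -0.207 | -0.020 | 0.000 |

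A similar illustrative simulation of abstinence, with selective retention and no true effect, gave a log-odds bias of about -0.12 to -0.15 under test-based selection, with type I error of 6.5 to 9.3%. As odds ratios, exp(-0.12) = 0.89 and exp(-0.15) = 0.86, where 1 is correct. Fixed adjustment gave about 0.01 to 0.02, with 5.2 to 6.0%.

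**3. Which planned models are exposed.** The primary outcome, depression, sleep, HIV risk and quality of life are tested by a group-by-time interaction with baseline as time 0 and a participant random intercept (Sections 6.2 and 6.3). In a linear version with complete data (145 per arm, four time points, assumed intraclass correlation 0.6), adding a covariate's main effect left the week-12 interaction estimate unchanged. At a covariate-outcome correlation of 0.5, power was 79.7% with no, fixed or test-selected adjustment. With 12% of follow-ups missing at random it was 75.9% under all three, and type I error was 5.0 to 5.7% across the correlations tried. In a rough negative binomial marginal model the standard error fell from 0.0708 to 0.0694, about 2%.

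Oral-fluid abstinence has no baseline value and is tested by a group contrast over weeks 4, 8 and 12 (Section 6.3). PGI has the same structure (Section 6.4). Check 2 therefore bears on abstinence, and on PGI only if a tertiary outcome is analysed in these sets; Section 6.6 mentions primary and secondary endpoints and subgroup analyses.

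**The case against.** The strongest reply is that the reach is small. Section 6.6 places these analyses after the primary analysis as supplements, and the complier analysis is only a possibility. The primary model does not use the rule, and the primary outcome already has a pre-specified five-variable adjusted analysis. Baseline days of use enter the primary model as the time-0 outcome, and Section 6.2 explains that the interaction allows for chance imbalance there. All of this stands.

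It can also be said that adjusting for differences in sets formed after randomisation is sensible. That stands as a reason to adjust for confounders, but not as a reason to find them by imbalance alone.

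Four stronger readings are tempting, and the documents do not support them.

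- A reader might infer that the Section 6.1 tests select the Section 6.6 covariates. They are the only between-arm baseline comparison the SAP describes, but it never states that link, and 6.6 does not say that the differences must be statistically significant.
- A reader might infer that chance alone picks the covariates. That describes the full randomised arms; in the per-protocol and complier sets imbalance can be systematic.
- A reader might infer a sizeable loss of power. Power differences of 8 to 10 points appear in a linear model with a single follow-up value, but the group-by-time models show almost none.
- A reader might infer that the tests generally lose their nominal level. In the group-by-time check they did not. The excess in the abstinence simulation is residual confounding under assumed selective retention.

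**Conclusion.** The concern holds for the supplementary analyses. Section 6.6 lets observed imbalance choose covariates after unblinding, although the same section names a prognostic list for the primary outcome. Section 6.1 separately plans baseline tests that serve no purpose between randomised arms.

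The effect falls mainly on the per-protocol and complier analyses of abstinence, where the illustrative bias is about -0.12 to -0.15 on the log-odds scale. For the group-by-time outcomes it is small or nil. The primary result is not affected.

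The figures rest on assumed correlations, selection strengths and a significance-based selector. Fixed adjustment removes the simulated bias because its list contains the variable that drives retention; unmeasured causes of discontinuation or non-adherence would remain. The 60 to 80% range is approximate because the number of tests is not stated and some Table 5 items overlap. The point merits a change of wording and does not threaten the trial's main conclusion.

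**What to change.** In the per-protocol and complier paragraphs of Section 6.6, replace the open reference to group differences with a list fixed before unblinding:

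- the five variables already named under Covariate adjustment;
- the stratification factors, which in practice adds site, since sex and the PHQ-9 score are among the five;
- any baseline predictors of discontinuation or adherence. Candidates can be sought in the pooled blinded data, where 85 of 339 treated participants discontinued, with others added on prior grounds because a predictor acting in one arm is diluted in pooled data.

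In Section 6.1, remove the inferential comparison and report baseline characteristics by arm without p-values. If allocation is already known, label any list chosen since then as post hoc.

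The cost is three sentences, and the five variables and the stratification factors are already collected. The models become slightly larger, and imbalance in unlisted variables is described but not adjusted for. For abstinence the list should stay short: Table 6 shows 31 + 33 + 36 = 100 negative results among the 797 samples then available, and the supplementary sets will hold fewer.

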## 6.2 Planned analysis of primary outcome

The analysis of the primary outcome will be based on the intention-to-treat dataset and based on unimputed data. All tests will be two-sided with  $p < 0.05$ .

Descriptive data on days of methamphetamine use will include the median number of days at each time point (baseline, week 4, week 8, week 12 and week 20), with interquartile ranges reported. Variance estimates (i.e., standard errors and confidence limits) will be bootstrapped.

The main effect of medication on days of methamphetamine use will be tested using a mixed model with a group (placebo [0] vs. mirtazapine [1]) by time (baseline [0], week 4 [1], week 8 [2], week 12 [3]) interaction effect, with time entered as a factor variable, producing individual effect estimates for each time point and making no assumptions about the linearity of changes over time. The primary timepoint is week 12. A negative binomial generalised linear mixed model will be used to test this effect. As noted under the general principles above, a random intercept term will be included in the model to account for clustering on repeats [31], and a random intercept term will be included in the model to account for site only if this significantly improves model fit (based on a likelihood ratio test;  $p < 0.05$ ).

Days of methamphetamine use in this model will be based on the past 28 days prior to baseline, and since the previous assessment at the week 4, 8 and 12 assessments (up to 35 days prior to the assessment). Days when the participant was incarcerated or hospitalised will be censored, as per the TLFB guidelines. An exposure term (i.e. offset) will be included in the model to adjust for the exact number of days in each of these periods, because this can vary depending on the actual assessment dates and censoring.

*Interpretation of the treatment effect from the model (i.e., interaction effect rate ratio):* The main treatment effect will be the time (baseline vs. active medication phase) x condition (active vs. placebo) interaction effect, with the primary timepoint being week 12. This interaction effect represents the rate ratio of change in days of methamphetamine from baseline to follow-up (i.e., rate of days of use at baseline/rate of days of use at follow-up) for the active condition, over the rate ratio of change from baseline to follow-up for the placebo condition. That is:

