#### **Depression**

The effect of mirtazapine on depression will be tested using a mixed model using a group (placebo [0] vs. mirtazapine [1]) by time (baseline [0] vs. weeks 4 [1], week 8 [2], week 12 [3]) interaction, with time entered as a factor variable, producing individual effect estimates for each time point and making no assumptions about the linearity of changes over time. The primary timepoint for this endpoint is week 12. A generalised linear mixed model will be used to test this effect.

The effect of mirtazapine on depression at week 20 will be tested using a separate analysis. We will test the main effect of the trial medication on depression at week 20 using a mixed model with a group (placebo [0] vs. mirtazapine [1]) by time (baseline [0], week 20 [1]) interaction effect. A generalised linear mixed model will be used to test this effect. We have chosen to analyse the week 20 endpoint separately because we believe that (a) differences in the conduct of the week 20 assessment may impact data variability (e.g., phone interviews and greater attrition), and (b) there are differences in the clinical interpretation of the outcome at the week 20 assessment (because participants are no longer on the trial intervention and are offered off-label mirtazapine and other substance use treatment prior to week 20).

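### A single participant intercept does not secure valid errors for the baseline-to-week-12 contrasts; the SAP should specify participant-clustered or participant-resampled errors, or an unstructured covariance, before unblinding

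*Combined protocol and SAP*

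**What the plan says.** **Correlation between visits.** Section 6.1 states: "A random intercept term for participant identifier will be included in all models with time-varying data model to account for clustering". Sections 6.2 to 6.4 add no random slope, no autoregressive or unstructured covariance and no robust standard error. A site intercept enters only if a likelihood ratio test supports it.

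**Primary outcome.** Section 6.2 fits group "by time (baseline [0], week 4 [1], week 8 [2], week 12 [3]) interaction effect, with time entered as a factor variable", with week 12 as the primary timepoint, and adds: "A negative binomial generalised linear mixed model will be used to test this effect".

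**Secondary and tertiary outcomes.** Section 6.3 gives depression the same four time points and says: "The primary timepoint for this endpoint is week 12". Sleep, HIV risk and quality of life follow the same pattern, as does anxiety in section 6.4. Other substance use also has week 12 as its primary timepoint, but its model includes week 20 as a fifth time point.

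**Variance estimation.** Section 6.2 says: "Variance estimates (i.e., standard errors and confidence limits) will be bootstrapped". The sentence closes the paragraph on descriptive medians. Section 6.1 says: "Bootstrapped confidence intervals will be used for outcomes that are highly skewed". That sentence closes a paragraph on descriptive statistics and baseline comparisons. Neither mentions the interaction coefficient, its p-value or the unit to be resampled.

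**Fallback.** Section 6.1 says: "If model assumptions are breached, other model options will be examined to identify the best model fit". These checks come after unblinding, and the examples given do not include the correlation structure.

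**The concern.** A random intercept imposes one common correlation between visits on the scale of the linear predictor, so the fit settles near the average over all pairs. In the four-visit models the primary contrast uses the two visits furthest apart. If participants resemble themselves less over twelve weeks than over four, the true baseline-to-week-12 correlation lies below that average. The variance of a change score is proportional to one minus the correlation, so a model-based standard error is then too small, the interval too narrow and the p-value too favourable. This would affect the confirmatory test and the four secondary outcomes assessed at week 12.

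**Working it through.** **1. The plan's own figures.** Section 3.3's attrition arithmetic reproduces: 255 / (1 − 0.25) = 340. The 90% power cannot be reproduced, because no dispersion, SD or within-participant correlation is given. Nothing elsewhere in the SAP supplies a correlation, so the values below are assumptions, shown as a range.

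**2. Linear models, closed form.** Inputs: four equally spaced visits (section 6.3), two-sided 0.05 (section 5.1), complete data, equal variances, AR(1) correlation ρ between adjacent visits (assumed). The six visit pairs comprise three at lag 1, two at lag 2 and one at lag 3.

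- Average correlation: m = (3ρ + 2ρ² + ρ³) / 6.
- Ratio of model SE to true SE for the week-12 contrast: q = √[(1 − m) / (1 − ρ³)].
- True alpha: 2 × [1 − Φ(1.96q)].

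| ρ | m | 1 − ρ³ | q | True alpha |
|---|---|---|---|---|
| 0.5 | 0.354 | 0.875 | 0.86 | 0.092 |
| 0.7 | 0.570 | 0.657 | 0.81 | 0.113 |
| 0.9 | 0.842 | 0.271 | 0.76 | 0.134 |

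The standard error is therefore 14% to 24% too small. If correlation is constant, m equals the baseline-to-week-12 correlation, q = 1 and alpha is 0.05.

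**3. Other substance use.** Week 20 brings in more distant pairs. In four-week units the ten pairs have lags 1 (three), 2 (three), 3 (two), 4 (one) and 5 (one). For ρ = 0.5, 0.7 and 0.9 this gives m = 0.259, 0.466 and 0.783; q = 0.92, 0.90 and 0.89; alpha = 0.071, 0.077 and 0.080. The effect is there but smaller.

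**4. Primary negative binomial model, simulation with no treatment effect.** 300 participants, complete data, 140 runs per scenario. Days were Binomial(28, p) with logit-normal p, set to resemble Table 6. The simulated quartiles were 18, 24 and 27 at baseline (Table 6: 17, 24, 28) and 9, 17 and 24 at week 12 (Table 6: 9, 17, 24). The planned random-intercept model was fitted by maximum likelihood. Correlations in the first column are on the logit scale; the second column gives the resulting correlation of observed days.

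| Assumed correlation | Baseline–week 12, observed | Model SE / empirical SD | Type I error, model SE | Type I error, participant-level robust SE |
|---|---|---|---|---|
| AR(1) 0.7 | 0.29 | 0.92 | 0.064 | 0.043 |
| AR(1) 0.9 | 0.63 | 0.86 | 0.086 | 0.036 |
| AR(1) 0.95 | 0.75 | 0.96 | 0.050 | 0.036 |
| 0.6 + 0.4 × 0.5^lag | 0.55 | 0.89 | 0.071 | 0.057 |
| 0.8 + 0.2 × 0.5^lag | 0.72 | 0.86 | 0.071 | 0.064 |
| Constant 0.6 | 0.51 | 1.06 | 0.021 | 0.043 |
| Constant 0.8 | 0.70 | 0.99 | 0.064 | 0.036 |

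With 140 runs the Monte Carlo standard error is about 0.02, so no single rate is precise. The pattern is consistent: the model SE is 4% to 14% too small in all five decaying scenarios and about right or slightly too large in the two constant ones. Participant-level errors stay at 0.04 to 0.06 throughout.

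**5. Which models are affected.** Abstinence and PGI average over weeks 4, 8 and 12 with no baseline contrast. The week-20 models for days of use and PHQ-9 have two time points, hence one correlation and no decay to misfit.

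**The case against.** The strongest reply is that the SAP nowhere says its errors will be model-based. Section 6.2 promises bootstrapped standard errors and confidence limits under the heading for the primary analysis, and medians with interquartile ranges hardly need standard errors. Table 6 presents PHQ-9, AIS-5, HRBS and EQ-5D as medians with IQR, the format section 6.1 keeps for highly skewed measures, so the general bootstrap rule could reach those outcomes too. This stands as far as it goes: a bootstrap that resamples participants and is applied to the interaction would remove the problem. But the SAP commits to neither part of that. Resampling rows rather than participants would not cure it. One analyst could report model-based Wald p-values and another participant-bootstrap intervals, both within the plan.

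It is also fair that the inflation depends on assumed correlations, and that the linear figures apply only where a linear model is fitted. Section 6.3 names a generalised linear mixed model without giving the family, and section 6.1 keeps linear models for normally distributed outcomes.

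A reader might infer three stronger things that the material does not support.

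- That the primary test has inflated error in fact. The documents contain no correlations and do not rule out the bootstrap. A separate simulation (339 participants, 14% dropout) gave 8% (37 of 438 runs) under one decaying pattern and 13% (250 runs) under another, whose baseline-to-week-12 correlation was 0.65. The independent runs above, at a similar 0.63, gave 0.086, so the 13% was not reproduced.
- That every repeated-measures model is affected. Step 5 shows otherwise.
- That the negative binomial model must be replaced because days are capped (Table 6 puts the baseline upper quartile at 28 of 28 days). That separate simulation held type I error at 4% under constant correlation, so the ceiling alone was not shown to harm the test. Replacing the model would also abandon the rate ratio on which sections 3.3 and 6.2 rely.

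**Conclusion.** The concern holds conditionally. The plan specifies one participant intercept for seven outcomes judged on a baseline-to-week-12 contrast, and its bootstrap sentences do not secure valid errors for that contrast. If errors are model-based and correlation decays, true alpha is about 0.09 to 0.13 in four-visit linear models (about 0.07 to 0.08 for other substance use, with its fifth visit) and about 0.05 to 0.09 in the primary model. If correlation is constant, it is nominal. The linear figures assume AR(1) decay, equal variances and complete data; the primary-model figures rest on simulated decay patterns and have Monte Carlo error of about two percentage points. The point should be settled before unblinding, because section 6.1 puts model checking and modification after it, when a change of covariance or error method would look driven by the result.

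**What to change.** Amend the SAP before unblinding:

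1. **Primary outcome.** State that the interaction rate ratio, its confidence interval and its p-value use participant-clustered robust errors, or a bootstrap that resamples whole participants. Keep the negative binomial model and the rate ratio.
2. **Continuous secondary and tertiary outcomes with a baseline-to-week-12 contrast.** Use an unstructured covariance over visits where the model is linear, and participant-clustered errors otherwise.
3. **Bootstrap sentences.** In sections 6.1 and 6.2, say whether they apply to the models or only to the descriptive summaries, and name the participant as the resampling unit.
4. **Site.** If the optional site intercept is retained, say how participant-level errors will then be obtained.

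The team can estimate visit-to-visit correlations now from the pooled blinded data, which would show how much this matters without revealing allocation. A binomial or beta-binomial model for days used out of days observed is at most an optional sensitivity analysis.

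The cost is a few sentences and standard software options. Intervals widen only if correlation decays. Relative to model-based ones, the increase is about 4% to 16% in the primary model (1/0.96 to 1/0.86) and 16% to 31% in four-visit linear models (1/0.859 to 1/0.765). That extra width is uncertainty the single-intercept model would have understated.
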